#### Motivation to change

The stages-of-change for physical activity behaviour change and for dietary behaviour change are assessed based on the five phases of the stage-of-change model [17]. These stages indicating whether a patient is in the precontemplation (not ready to change), contemplation (thinking about possible change), preparation (preparing to change), action (carrying out changed behaviour) or maintenance phase (maintaining changes behaviour).

#### Cost-effectiveness parameters

Care consumption is estimated with the Dutch care consumption questionnaire [41], which is adapted to the context of the current study. Use of medication is derived from patient record forms. Quality adjusted life years (QALYs) will be the primary outcome measure in the cost-effectiveness analysis. In order to estimate QALYs, utility scores will be derived from the SF12, using the SF6D algorithm [42, 43].

#### Physical fitness

All patients of one organisation (GGZ Friesland) are invited to wear a pedometer (Yamax SW200 [44]) for at least seven days, reporting the total steps per day in a diary. A trained research assistant measures patients’ body fat percentage in standing position [45] by bioelectrical impedance analysis (BIA) in triplicate using a single-frequency bioimpedance analyzer (Model BIA 101, AKERN Srl, Italy) [46, 47]. In order to calculate the body fat percentage using a formula, height and weight are measured in accordance with previously described methods.

#### Web tool evaluation

After the intervention, participants’ perception of and satisfaction with the web tool is assessed by a questionnaire.

### Measurements on staff level

Staff members receive an online questionnaire at baseline and after the intervention is finished to gather information on, among other things, own lifestyle behaviours, attitudes towards lifestyle and process evaluations as potential determinants influencing intervention implementation. Data on birth year, level of education and experience are only collected at baseline.

#### Knowledge on diet and physical activity

Staff members answer questions to rate their knowledge on physical activity and diet, based on national guidelines regarding physical activity [48] and diet [40].

Attitudes, self-efficacy and frequency of performing lifestyle related activities. The questionnaire also addresses staff members’ attitudes toward lifestyle coaching for patients, rate their self-efficacy in lifestyle coaching and rate how often they perform lifestyle related activities with/for patients and the difficulty they experience with these activities [49]. Questions on attitude and self-efficacy are based on the ACE-model which describes the relationship between a persons’ attitudes, social influences and self-efficacy, and their behaviour. Questions are adapted to fit the study design and patient group [50, 51]

#### Lifestyle habits

Staff members’ daily physical activity is assessed with the SQUASH questionnaire [39] and their diet is assessed using a semi-quantitative food frequency questionnaire (FFQ) with items based on a screening questionnaire for healthy eating habits of the Netherlands Nutrition Center according to the Dutch guidelines for a healthy diet [40].

#### Web tool evaluation

After the intervention, nurses fill in a questionnaire about how they perceived working with the web tool.

### Statistical analysis

Variables will be presented as mean ± standard deviation (SD), and if not normally distributed as median [25th-75th percentiles], or N (%) for frequencies. Missing data are handled differently based on amount and type of missingness. If missing data can be well predicted by regression methods, multiple imputation will be considered. Otherwise, interpolation or replacement by study mean or median will be preferred over complete case analyses.

The primary outcome is the change in waist circumference (in cm) over time (from baseline to six and from baseline to twelve months) comparing the intervention group to the control group. This will be analysed with multilevel linear mixed models using teams as cluster. Analysis will be based on intention-to-treat principle. In per-protocol analyses, the intervention effect on cardiometabolic risk factors will be studied as described above, comparing participants with different degrees of intervention adherence to controls. Secondary study outcomes are analysed according to the same principles and techniques as the primary outcome. A priori sensitivity analyses are foreseen for participants’ age, gender and type of housing. In additional analyses, we will test whether the 12-months lifestyle intervention changes the level of motivation (stage-of-change) for changing diet of physical activity levels. An alpha of 0.05 is considered statistically significant.

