### Participants

The study population consists of community-dwelling SMI patients and SMI patients living in sheltered facilities. Of this population, approximately 75% of the patients is diagnosed with a psychotic disorder, 15% with bipolar disorder and approximately 10% with complex personality disorders. In the North of the Netherlands, SMI patients are invited for annual Routine Outcome Monitoring screenings as part of standard care, consisting of a physical examination, a lab test and psychosocial measures. Patients are invited for the LION study when ROM screening outcomes indicate at least one of the following risk factors for metabolic syndrome: waist circumference > 88/102 cm (females/males); fasting glucose > 5.6 mmol/L or HbA1c > 5.7%; BMI > 25 kg/m^2^. Exclusion criteria are being pregnant, a BMI < 19 kg/m^2^, being primarily diagnosed with Korsakov syndrome or having a physical impairment which makes daily physical activity impossible. When patients are eligible for the study, they receive a detailed information letter from their case manager and, if willing to participate, sign informed consent.

The main objective of this trial is to detect an abdominal weight loss having public health significance. Previous work has indicated that 5-10 cm reduction in waist circumference (WC) is considered a realistic guideline with a high probability of health benefits [32]. For power calculations, we assumed 10% dropout rate. To include 250 participants, a 10% extra will be needed resulting in a total of 275 patients. Under these assumptions, and assuming an SD of 16.3 cm based on pilot data from this population, for two-sided 0.05-level tests of the null hypothesis, the study should provide approximately 80% power for detecting a difference of 5.8 cm in WC at 12 months between intervention and control groups. In addition, the study will have the same power to detect a reduction of 0.6 mmol/L in plasma glucose, given an SD of 1.7 mmol/L.

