### Outcomes

Measurements are performed on patient and staff level. An overview of all measurements at baseline, six and twelve months is given in Table 4.

**Table 4 Tab4:** LION trial measurement overview

		Baseline	6 months	12 months
Measurements on patient level				
Routine Outcome Monitoring				
General information	Birth year, gender, diagnoses, year of first psychosis	X		
	Medication use	X		X
Physical measures	Height	X	X	X
	Weight	X	X	X
	Waist circumference	X	X	X
	Blood pressure (systolic, diastolic, pulse)	X	X	X
Lab test	Lipids (Total cholesterol, LDL-cholesterol, HDL-cholesterol, triglycerides)	X	X	X
	Glucose metabolism (glucose, HbA1c)	X	X	X
Psychological measures^b^	CDSS	X		X
	PANSS	X		X
	HoNOS	X		X
	MANSA	X		X
Cost-effectiveness^a^	Dutch care consumption questionnaire	X	X	X
	SF6D	X	X	X
Web tool TLM				
Lifestyle habits	Daily physical activity (SQUASH)	X	X	X
	Food frequency questionnaire (adapted to patient population)	X	X	X
Additional measure by research assistant				
	Physical activity (pedometers) and body fatness^c^	X	X	X
Measurements on staff level				
General information	Birth year, gender, level of education, number of years working in psychiatry, function	X		
Staff questionnaire	Knowledge on diet and physical activity, attitude towards lifestyle changes in patients, self-efficacy in addressing lifestyle issues with patients	X		X
	Daily physical activity (SQUASH)	X		X
	Food frequency questionnaire	X		X

^a^ Measures are not part of standard ROM screening but added to ROM screening for the purpose of this study. ^b^ The conducted psychosocial measures within the ROM protocol could vary per team, not all teams conduct every psychosocial measure. ^c^ Only conducted by one of the five health care organisations (GGZ Friesland)

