### Potential risks for bias

Some potential risks for bias might be expected. First, although patient selection bias should be minimal, it is still possible that it is difficult for nurses to include patients that are unmotivated to change their lifestyles in a lifestyle intervention study. Motivated patients are expected to be more easily included, leading towards patient selection bias based on the level of motivation. Second, because patients determine which lifestyle behaviours they wish to change, it is possible that they target other somatic health outcomes (e.g. dental health, sleeping patterns) than the primary study outcome waist circumferences and other cardiometabolic risk factors. In this case, stating that the intervention does not seem effective in reducing the primary outcome might be a biased conclusion when patients wished to change other health outcomes and might have been successful in addressing these changes. Third, although ROM is implemented on all sites, it is possible that not all sites have the capacity to conduct all measures, leading to missing values. In addition, ROM nurses cannot collect blood samples themselves but send patients an invitation to visit a (hospital) laboratory. Although ROM nurses convince and remind patients to do so, patients might be reluctant to go to the laboratory, also leading to possible missing values.

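### The missing-data fallback allows outcomes to be filled with the pooled study mean or median, which shrinks the treatment effect by the missing fraction when missingness is similar in both arms

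*Protocol article*

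**What the plan says.** The rule is in the protocol article, Statistical analysis, and has two steps. The first is "If missing data can be well predicted by regression methods, multiple imputation will be considered". The second is that, failing this, "interpolation or replacement by study mean or median will be preferred over complete case analyses". The handling is said to depend on the amount and type of missingness, but no variable is assigned to a method and no outcome is excluded.

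The same section defines the endpoint: "The primary outcome is the change in waist circumference (in cm) over time", from baseline to six and to twelve months. Of the model it says "This will be analysed with multilevel linear mixed models using teams as cluster". Secondary outcomes follow the same principles.

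On how much will be missing, Participants assumes 10% dropout. Potential risks for bias adds that some sites may lack capacity for all measures and that "patients might be reluctant to go to the laboratory, also leading to possible missing values". A footnote to Table 4 (Outcomes) notes that "not all teams conduct every psychosocial measure". No percentage is given beyond the 10%.

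**The concern.** A study mean or median is the same number for both arms. Patients filled in with it contribute no treatment difference, so the estimate is diluted. The filled values are then counted as observations, so the interval carries no uncertainty for them.

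The trigger is also the wrong way round. The constant is used when prediction is poor, whereas multiple imputation would carry poor prediction into a wider interval.

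The comparison with complete-case analysis leaves out the obvious third option. A mixed model for the 6- and 12-month values can use every observed visit without filling in any outcome. What is at stake is the size of the reported effect on waist circumference, and on every secondary outcome handled the same way, together with the validity of its confidence interval.

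**Working it through.** **Inputs from the protocol article (Participants):** difference 5.8 cm, SD 16.3 cm, 250 evaluable of 275, 10% dropout, and alpha as in "for two-sided 0.05-level tests of the null hypothesis". **Assumed:** 1:1 allocation, no team clustering, missing shares of 20% and 30%, and a baseline-to-12-month correlation of 0.8–0.9 where one is needed. The article gives neither a correlation nor an intracluster correlation.

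**The plan's own figure.** With 125 per arm, SE = 16.3 × √(2/125) = 2.06. Power = Φ(5.8/2.06 − 1.96) = Φ(0.85) = 0.80. The stated 80% is reproduced.

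**Pooled-mean replacement, 12-month value.** Take n = 275/2 = 137.5 per arm and a share m missing completely at random in each arm.
- Expected estimate = (1 − m) × 5.8.
- SE of the filled-in analysis ≈ 16.3 × √(2(1 − m)/n).
- SE from observed values = 16.3 × √(2/(n(1 − m))).
- Coverage of the true 5.8 cm = Φ(1.96 − b) − Φ(−1.96 − b), where b = 5.8m / SE of the filled-in analysis.

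| m | Estimate (cm) | SE filled in | SE observed | b | Coverage |
|---|---|---|---|---|---|
| 10% | 5.22 | 1.87 | 2.07 | 0.31 | 94% |
| 20% | 4.64 | 1.76 | 2.20 | 0.66 | 90% |
| 30% | 4.06 | 1.65 | 2.35 | 1.06 | 82% |

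None of these figures uses a correlation. The ratio of estimate to SE is unchanged: at 30%, 4.06/1.645 = 5.8/2.350 = 2.47. In this analysis the test therefore loses nothing; the damage is to the estimate and the interval.

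**Other analyses (simulation, equal missingness in both arms, completely at random).** The shrinkage is the same; coverage is as follows.
- Baseline-adjusted, correlation 0.8: about 92% at 10% missing and 70% at 30%.
- Change score with the 12-month level replaced, correlation 0.8–0.9: about 92–93%, 82–88% and 74–79% at 10%, 20% and 30%.
- Change itself replaced, same correlations: about 89–93%, 67–82% and 36–61%.
- Baseline-adjusted analysis of observed values: unbiased, with coverage of about 94–95%.

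Median replacement behaves almost identically. With no true effect and equal, completely random missingness, the type I error of mean replacement stays at 0.043–0.060.

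**Unequal missingness.** The case is 10% missing in one arm and 30% in the other, heavier patients missing more often, correlation 0.8, baseline-adjusted. Mean replacement gives −6.1 cm for a true −5.8, and −1.6 cm for a true zero with 25% rejection. Observed-value analysis gives −5.8 and 0.0, with 5% rejection. If the same unequal shares are missing completely at random, mean replacement gives −4.6 for a true −5.8. The bias can therefore go either way.

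**Interpolating a missing 6-month value.** Expected 6-month effect = (1 − m) × d6 + m × d12/2. With d12 = 5.8 and m = 0.3 the second term is 0.87. A true d6 of 2.9 stays 2.9; 5.8 becomes 4.93; 4.0 becomes 3.67; 1.0 becomes 1.57. A missing 12-month value has no later value to interpolate to.

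**The case against.** The best defence is that the fallback is conditional. Multiple imputation comes first, and at a correlation of 0.8–0.9 baseline alone explains 64–81% of the 12-month variance (0.8² to 0.9²). Waist circumference would then probably count as well predicted and not reach the fallback. This stands as a limit on the coverage figures that use those correlations. It does not rescue the rule. Multiple imputation is only to be considered, and the (1 − m) shrinkage and the final-value coverage need no correlation, so they apply equally where prediction is poor.

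A second defence is that the article gives only 10% dropout and describes further missing values as possible. That also stands: at 10% the harm is modest. A statistical analysis plan may refine the rule, but the article positively ranks the method, so this is not a detail left out.

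A reader might infer more than the documents support:
- *The whole rule pulls towards zero.* Interpolation may be unbiased or err either way, and unequal missingness can move mean replacement away from zero.
- *Standard errors are always too small.* In the change-score analysis at 30% missing the SE is 1.51 against 1.49 for observed values.
- *The trial loses its power.* A marked loss (90% to about 73% at 10% missing) appears only for an assumed 3 cm effect at correlation 0.9 with the level replaced. At the design's 5.8 cm the same set-up keeps 97.5–99.8% at 10% missing and 89–96% at 20%.
- *Scales not collected by a team will be filled with a constant.* The article does not say so; it merely does not rule it out. Distortion of between-team variation was not calculated.

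**Conclusion.** The rule is wrong as written for outcome variables. Pooled mean or median replacement with similar missingness by arm multiplies the expected effect by (1 − m). At the protocol's own 10% dropout this costs about 0.6 cm of 5.8 cm, with coverage of about 90–94% depending on model and correlation. At 20% and 30% missing the loss is about 1.2 and 1.7 cm, with final-value coverage of about 90% and 82% and lower coverage for change scores at high correlation.

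With equal, completely random missingness the defect is bias and undercoverage, not false positives. With missingness that differs by arm and depends on waist size, false positives are also possible. The results rest on 1:1 allocation and no clustering; the 20–30% shares and the correlations are assumptions, not figures from the article.

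**What to change.** - Delete interpolation and mean or median replacement for all outcome variables.
- Make the planned multilevel mixed model the primary analysis, fitted to all observed 6- and 12-month values with baseline in the model and team as cluster. It is valid under missing at random and needs no outcome imputation.
- Use multilevel multiple imputation as a sensitivity analysis. Imputing by arm and adding a shift analysis for data not missing at random are useful options but not essential to this point.
- State that a scale some teams do not collect is analysed only in the teams that collect it.

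The cost is a change of wording and a little more analysis work. No new data are needed.

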### Study setting

Mental health care for severe mentally ill (SMI) outpatients is organized by a Flexible Assertive Community Treatment (FACT) team with MH nurses. FACT means that patient care is outreaching, takes place in the community (patients’ own environment) and ranges from high intensive (24 h) treatment to low intension support – for a detailed description of FACT, see [30, 31]. Patients living in sheltered facilities receive a combination of housing and services in the community. 21 FACT and eight sheltered facility teams serving SMI patients of five mental health care organizations in the North of the Netherlands, an area covering 2.8 million inhabitants, are invited for this study. Per team, nurses are invited to participate. All teams per organization are matched based on caseload size, mean age of patients, mean duration of admission of patients, most frequent diagnosis and location (urban or rural). After matching, teams are randomly allocated to the control or intervention arm by means of a random number generator by a researcher of the research team not involved in training of staff and recruitment of patients (see Fig. 1 for flowchart of the study). To minimise spill-over, randomisation is on team level, although inclusion of study participants and statistical inference are on patient level.

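### The 5.8 cm detectable difference belongs to a comparison of 12-month waist, not to the planned team-clustered analysis of change, and that analysis mentions no adjustment for baseline waist.

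*Protocol article*

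**What the plan says.** On the outcome, the Statistical analysis section states: "The primary outcome is the change in waist circumference (in cm) over time (from baseline to six and from baseline to twelve months"), comparing the two arms. On the model it says: "This will be analysed with multilevel linear mixed models using teams as cluster". It lists no fixed effects. Baseline waist as a covariate and a patient level are neither included nor excluded. Secondary outcomes are to be analysed in the same way.

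Table 4 schedules waist at baseline, 6 and 12 months.

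The power statement in the Participants section covers a different quantity: "approximately 80% power for detecting a difference of 5.8 cm in WC at 12 months between intervention and control groups", "for two-sided 0.05-level tests of the null hypothesis" and "assuming an SD of 16.3 cm based on pilot data from this population". It does not say whether that SD is of waist or of change in waist. The size used is given as: "To include 250 participants, a 10% extra will be needed resulting in a total of 275 patients". The Discussion subsection on changes in study design says that clustering was no longer allowed for in the sample size.

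**The concern.** The power statement and the primary analysis should describe the same comparison. Here one concerns waist at 12 months and the other concerns change from baseline. The precision of a change analysis depends on the within-patient correlation between baseline and 12 months, which the article does not give. The planned model also includes a team effect, which the power figure leaves out. The reader therefore cannot tell what difference the primary test can detect.

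This bears on how a null result is read. The Participants section treats a waist reduction of 5 to 10 cm as realistic and beneficial. The stated 5.8 cm lies inside that range, whereas the planned analysis may be able to detect less than 5 cm.

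The second matter is efficiency. Baseline waist is already collected, and using it as a covariate gives a more precise estimate than unadjusted change. It also removes the part of a chance baseline difference that change scores carry, which is useful when at most 29 teams are randomised.

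**Working it through.** **Inputs from the article.** SD 16.3 cm, difference 5.8 cm, two-sided alpha 0.05, 250 patients for analysis (Participants); 29 teams invited, 21 plus 8 (Study setting).

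**Assumptions.** 1:1 allocation of patients (the ratio is not stated); equal variances at baseline and 12 months; correlation r between baseline and 12-month waist from 0.5 to 0.9; ICC from 0.01 to 0.05. The article gives neither r nor an ICC.

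**Step 1: reproduce the stated figure.** Detectable difference at 80% power = (1.960 + 0.842) × SD × √(4/N) = 2.802 × 16.3 × √(4/250) = 5.78 cm. Power for 5.8 cm with 125 per arm is 80.3% (80.0% with the noncentral t). No baseline correlation and no design effect enters, so this is a plain two-sample comparison of 12-month waist.

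**Step 2: the change and baseline-adjusted analyses, if 16.3 cm is the SD of waist.** SD of change = 16.3 × √(2(1 − r)). SD after baseline adjustment = 16.3 × √(1 − r²). Each goes into the Step 1 formula, still without clustering.

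| r | SD of change (cm) | adjusted SD (cm) | detectable, change (cm) | detectable, adjusted (cm) |
|---|---|---|---|---|
| 0.5 | 16.30 | 14.12 | 5.78 | 5.00 |
| 0.7 | 12.63 | 11.64 | 4.47 | 4.13 |
| 0.8 | 10.31 | 9.78 | 3.65 | 3.47 |
| 0.9 | 7.29 | 7.11 | 2.58 | 2.52 |

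The change analysis gives the stated figure only at r = 0.5. Below that it does worse: 6.83 cm at r = 0.3.

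**Step 3: size of the gain from adjustment.** Variance of change divided by adjusted variance = 2(1 − r)/(1 − r²) = 2/(1 + r), or 1.33, 1.18, 1.11 and 1.05 at r = 0.5, 0.7, 0.8 and 0.9. Adjustment therefore removes (1 − r)/2 of the variance: 25%, 15%, 10% and 5%.

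**Step 4: chance baseline difference.** At an assumed ICC of 0.03 the design effect is 1 + (8.62 − 1) × 0.03 = 1.23. The SE of the baseline difference between arms is then 16.3 × √(4 × 1.23/250) = 2.29 cm. Unadjusted change carries (1 − r) of whatever difference arises. At r = 0.8 that is 0.2 × 2.29 = 0.46 cm for a difference of one SE. This calculation makes no allowance for the matching of teams.

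**Step 5: clustering.** Patients per team = 250/29 = 8.62. Design effect = 1 + 7.62 × ICC = 1.08 at ICC 0.01 and 1.38 at ICC 0.05. For the comparison that was powered, 5.78 cm becomes 6.00 to 6.79 cm, and power for 5.8 cm falls to 77% to 67%. With the same design effects applied to change, the detectable difference is 3.79 to 4.29 cm at r = 0.8 and 2.68 to 3.04 cm at r = 0.9. The two omissions cancel where 2(1 − r) × design effect = 1. At r = 0.7 that is a design effect of 1.67, an ICC of about 0.09.

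**Step 6: the other reading of 16.3 cm.** If it is an SD of change, 5.78 cm is correct for the change analysis before clustering. The implied SD of waist at r = 0.8 would then be 16.3/√0.4 = 25.8 cm. That makes this reading less likely but does not rule it out.

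**The case against.** The strongest reply is that this is a condensed article. Covariates, random effects and covariance structure are commonly left to an analysis plan that is not shown, and defining the outcome as change does not rule out adjusting for baseline. Sizing on the SD of the outcome without credit for baseline correlation is a familiar and cautious simplification. For r above 0.5, 5.8 cm is conservative before clustering, and the further gain from a baseline covariate is only about 0.3 to 0.1 cm at r = 0.7 to 0.9.

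Most of this stands. It limits the point to a mismatch between two stated passages and an improvement to the model.

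Three stronger readings are tempting, and the documents support none of them:

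- **That the plan leaves out a patient level.** Team is the only cluster named, but the text does not say it is the only level. The wording is compatible with a patient term.
- **That the standard errors will be far too wide.** This would follow only if the three raw waist values per patient were fitted with no patient term. The article does not prescribe such a fit, and it names change as the outcome. With 12-month change alone there is one value per patient, and a team intercept is adequate.
- **That change scores are biased.** Under randomisation they are unbiased on average, and their standard error already reflects chance imbalance. Adjustment improves precision and deals with the imbalance that happens to occur. Teams are also matched before allocation.

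The reply does not remove the mismatch, because both the outcome and the power statement are fixed in the article itself.

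**Conclusion.** The point holds in limited form. The stated 5.8 cm is correct arithmetic for an unadjusted, unclustered comparison of 12-month waist, and it does not describe the team-clustered analysis of change. How far it is out, and in which direction, depends on what 16.3 cm refers to and on an r and an ICC that the article does not give. Read as the SD of waist, with r of 0.7 to 0.9, the change analysis would detect about 4.5 to 2.6 cm before clustering, and clustering takes back part of that. A reader should not conclude that the trial is underpowered, or that it has power to spare, from this mismatch alone.

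The article does not mention baseline adjustment. Including it would be a modest gain with no apparent drawback: 15% to 5% less variance than unadjusted change at r = 0.7 to 0.9, and 25% less at r = 0.5.

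**What to change.** In the Statistical analysis section, include baseline waist as a covariate, with a baseline-by-visit term, in the team-clustered model. State that within-patient correlation is modelled when the 6- and 12-month visits are analysed together. Use the same form for the other outcomes measured at baseline.

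In the Participants section, say whether 16.3 cm is the SD of waist or of change in waist. Restate the detectable difference for the planned model over a stated range of r and ICC.

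The cost is wording and a short recalculation. Baseline waist is already scheduled, so no new data are needed.
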